**Methods:**

The alpha-i will be refined using information from focus groups and surveys conducted with small business owners and managers, YPAO providers, and parents and guardians of the youths from low-income, predominantly minority neighborhoods. A cluster randomized controlled trial will then be conducted for 1 year to examine the effects of the refined intervention (beta-i) on small business support for YPAOs in 10 low-income, minority neighborhoods. The control group of neighborhoods (n=10) will be provided with a standard practice intervention. The primary outcome for aim 2 will be the percentage of small businesses not supporting YPAOs at baseline that subsequently provide support for YPAOs at follow-up. We also will consider the US dollar equivalent of all types of support (monetary, goods/services, and time) donated for YPAOs by small businesses. In addition, we will examine the impact of the increased small business support for YPAOs on YPAO utilization by the youth.

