Small businesses (<500 employees) represent 99.64% (27.9/28.0 million) of all businesses operating in the United States. Total revenues typically exceed US $1 trillion annually and over half a million new businesses start each month [57]. More than one-fifth of small businesses are minority-owned with revenues totaling nearly US $700 billion [58]. Established philanthropic principles have been used to explain behaviors of different types of entities including small businesses [59-66]. Event sponsorship or sponsorship marketing refers to supporting various types of initiatives ranging from educational partnerships to YPAOs [59]. Small businesses heavily engage in event sponsorship compared with large businesses and they prefer to contribute to events connected to their local neighborhood [60-62,64]. It allows them to reach their target market more efficiently, expose their product/service directly to the market, give back to the neighborhood that supports them, and present an image of a socially responsible organization [63]. These actions can lead to increased consumer support and ultimately greater revenue [65,66]. Not surprisingly, when small businesses decide to support an initiative, they tend to sustain that support [67].

The strong preference by small businesses for sponsoring local programs sets up a powerful force that, if utilized effectively, would have a dramatic and lasting impact on the quantity and quality of YPAOs and, ultimately, physical activity and health in low-income, minority neighborhoods. Supporting this contention are findings from our preliminary study showing that although a majority of small businesses do not currently support YPAOs (~60%), a large percentage (88%) of these non-YPAO supporters believe they should [67,68].

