#### Power Analysis

Our power analysis was based on the percent change in the proportion of small businesses supporting YPAOs at baseline that subsequently provided support for YPAOs during the intervention. Data to construct the primary outcome will be derived from tracking donations and small business surveys. Power formulas accounted for experimental condition, number of neighborhoods, number of businesses/neighborhoods surveyed, variance estimates of the outcome measure from preliminary studies, and a conservative estimate of the intraclass correlation coefficient (ICC). In our previous research, a 27% versus 8.0% increase in support for community physical activity initiatives by small businesses not supporting them at baseline was observed in the treatment and the control neighborhoods, respectively [78]. On the basis of our previous experience conducting research in neighborhoods and our desire to develop a sufficiently rich and diverse dataset, we tested whether 10 neighborhoods per condition would also provide sufficient statistical power for our primary outcome. Thus, the final power model was based on 10 neighborhoods per condition, 10 small businesses nested in each neighborhood, a difference in proportions of 19 percentage points, and an ICC of 0.05. It was determined that having 10 neighborhoods per condition would give us a statistical power of 86% to yield a statistically significant result. In a previous study, we completed interviews at 66.2% (98/148) of the small businesses visited [67]. Of them, 30.4% (45/148) refused and interviews could not be completed with an eligible individual at 3.4% (5/148) of businesses. For the proposed study, we expect an average of 50 small businesses per neighborhood or 500 per condition. Therefore, we will obtain a random sample at baseline of 185 small businesses per condition and expect to complete a baseline survey at 66.2% (122/185) per condition. Of these 122, we expect a loss-to-follow-up of 15% to 17%, giving us 104 businesses per condition or ~10 per neighborhood. This will allow us to achieve our goal of interviewing no less than 20% of the eligible businesses and obtaining a representative sample [84].

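### The 86% power counts all 10 surveyed businesses per neighborhood, but only baseline non-supporters (about 60%) can contribute to the primary outcome; the design gives about 67–72%

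*Protocol article*

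**What the plan says.** The abstract (Methods) gives the primary outcome of aim 2 as "the percentage of small businesses not supporting YPAOs at baseline that subsequently provide support for YPAOs at follow-up".

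The Power Analysis section takes its effect from earlier work that observed "a 27% versus 8.0% increase in support for community physical activity initiatives by small businesses not supporting them at baseline". The model it reports has 10 neighborhoods per condition, "10 small businesses nested in each neighborhood, a difference in proportions of 19 percentage points, and an ICC of 0.05", and the resulting power is given as 86%.

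The same section then derives the businesses to be surveyed. It expects 500 small businesses per condition, samples 185 at random, surveys 122 at baseline (66.2%), and loses 15% to 17% to follow-up, "giving us 104 businesses per condition or ~10 per neighborhood".

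The Background section reports from preliminary work that "although a majority of small businesses do not currently support YPAOs (~60" (a percentage). The Results section reports 244 completed baseline surveys, that is 2 × 122, and mentions no restriction to non-supporters.

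The Power Analysis section also opens by describing the outcome as the change in "the proportion of small businesses supporting YPAOs at baseline that subsequently provided support for YPAOs during the intervention", which is the opposite group from the one in the abstract.

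**The concern.** The effect size and the primary outcome both belong to businesses that were not supporting at baseline. The cluster size of 10 belongs to all surveyed businesses. The chain from 500 to 104 per condition allows for non-response and attrition but not for businesses that already give support. Those businesses cannot become new supporters, so they drop out of the denominator. The section's goal of interviewing at least 20% of eligible businesses confirms that all businesses are the base: 104/500 = 20.8%.

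Power for the primary hypothesis is therefore overstated. A non-significant result would be read as coming from a trial with a 14% chance of missing a 19-point effect, when the real chance is about twice that.

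**Working it through.** **Inputs**
- Rates 27% and 8%, 10 neighborhoods per condition, ICC 0.05, 10 businesses per neighborhood, stated power 86%: Power Analysis.
- Non-supporter share about 60%: Background.
- 122 surveyed per condition, 15–17% lost: Power Analysis.
- Two-sided alpha 0.05: assumed, as the article does not state it.

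**Formulas** (m = contributing businesses per neighborhood)
- Design effect: DE = 1 + (m − 1) × 0.05
- Effective number per condition: n = 10m / DE
- SE = √[(0.27 × 0.73 + 0.08 × 0.92) / n] = √(0.2707 / n)
- Power (z) = Φ(0.19/SE − 1.96); power (t) uses the noncentral t with noncentrality 0.19/SE

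**Step 1: reproduce the stated figure (m = 10).** DE = 1.45; n = 100/1.45 = 68.97; SE = 0.0627; 0.19/SE = 3.03. Power is 85.8%, which matches 86%. An arcsine test gives 86.2% and a pooled-variance test 84.3%. The stated figure therefore uses all 10 businesses. It also uses a normal critical value: a t reference on 18 df (20 neighborhoods minus 2) gives 81.8% on the same inputs.

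**Step 2: count those who can contribute.** 122 × 0.6 × 0.83 = 60.8 and 122 × 0.6 × 0.85 = 62.2 per condition, or about 6 per neighborhood.

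**Step 3: recompute (m = 6).** DE = 1.25; n = 60/1.25 = 48.0; SE = 0.0751; 0.19/SE = 2.53.

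| Reference | m = 10 | m = 6 |
|---|---|---|
| Normal | 85.8% | 71.6% |
| t, 18 df | 81.8% | 66.8% |
| t, 9 df (10 pairs) | 77.0% | 61.6% |

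A beta-binomial simulation (20,000 runs) with a t-test on neighborhood proportions gives 67% at m = 6, and 65% when the number of non-supporters varies as Binomial(10, 0.6).

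**Step 4: vary the non-supporter share** (of 10 followed per neighborhood).

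| Share | m | Normal | t, 18 df |
|---|---|---|---|
| 50% | 5 | 65% | 61% |
| 60% | 6 | 72% | 67% |
| 70% | 7 | 76% | 72% |
| 80% | 8 | 80% | 76% |

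Starting from 104 rather than 100 per condition raises these by 1 to 2 points: 67–78% (normal) and 62–73% (t) for shares of 50–70%.

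**Step 5: detectable difference.** With m = 6 and 8% in controls, 80% power needs a difference of about 21.5 points (normal) or 23 points (t, 18 df).

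**Step 6: other readings of the outcome group.**
- All businesses, with only non-supporters changing: the difference dilutes to 0.6 × 19 = 11.4 points (0.4 + 0.6 × 0.27 = 56.2% against 0.4 + 0.6 × 0.08 = 44.8%). Power is about 25–27% at m = 10.
- Baseline supporters, as the Power Analysis section literally says: about 4 per neighborhood. Power is about 58% (normal) even if the difference were 19 points.

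**The case against.** The strongest objection is that the size of the shortfall rests on one soft input. The 60% is a preliminary estimate, not this trial's baseline, and the Background does not say that it came from neighborhoods like these. That stands, so the 67–72% is conditional on it. The direction does not depend on it: any share below 100% gives less than the stated inputs do, and an 80% share gives 80% with a normal critical value.

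The Power Analysis section says that the outcome also draws on tracked donations. A baseline non-supporter who gives to the fund could then be classified without a follow-up survey. At the upper bound, with no attrition, 122 × 0.6 = 73 per condition (m about 7.3) gives 77.7% (normal) or 73.1% (t, 18 df). This narrows the gap but does not close it, and support given outside the fund would still need the survey.

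The choice of degrees of freedom is a separate and smaller matter, and an article may leave it to the analysis plan. That is fair: the denominator alone costs about 14 points (85.8% to 71.6%) on the article's own normal basis. The 9-df figure applies only if the analysis respects the pairs, which the Approach to Analysis section does not describe.

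An ICC of 0.05 is called conservative. Even with an ICC of 0, m = 6 gives 80.7% (normal) or 76.3% (t, 18 df).

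Finally, this is called a pilot study. It nonetheless states a power for its primary outcome and poses hypotheses of significant difference, so the figure should be right.

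**Conclusion.** The concern holds. The 86% is reproduced only by counting every surveyed business, while the effect size and the outcome are confined to baseline non-supporters. At the article's own share of about 60%, power for a 19-point difference is about 72% with a normal critical value and about 67% with a t reference on 18 df. The chance of missing the effect is then 28–33% instead of 14%. This assumes two-sided 5%, an ICC of 0.05, 10 neighborhoods per condition and about 6 non-supporters followed in each. None of the alternatives tried for the share, attrition, ICC or outcome group restores 86%.

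**What to change.** 1. Settle the outcome group first. The abstract says non-supporters, the opening of the Power Analysis section says supporters, and Hypothesis 1 speaks of small businesses overall. State one definition and use it throughout.
2. Restate the power for that denominator. Baseline surveys are complete, so use the observed number of non-supporters per neighborhood, less expected attrition, with 10 neighborhoods per condition, ICC 0.05 and a t reference on the cluster degrees of freedom. State alpha and sidedness.
3. If the observed share is near 60%, the statement would be about 67% power for 19 points, or 80% power for about 23 points.

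The cost is a rewritten power paragraph and a less favorable figure, with no extra businesses. For comparison, having 10 non-supporters per neighborhood at follow-up would have needed about 100/0.6 = 167 followed per condition. That means 167/0.85 to 167/0.83 = 196 to 201 surveyed at baseline and, at 66.2% completion, about 296 to 303 sampled, against 104, 122 and 185 planned.

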### Objectives

In accordance with the socioecological model and established philanthropic principles, we developed an alpha version of an intervention (alpha-i) for increasing small businesses’ involvement with YPAOs. We are now poised to create a beta version (beta-i) and conduct a pilot study of its *impact* on small business support for YPAOs and *YPAO utilization by the youth* in low-income, minority neighborhoods. To meet this objective, we will complete the following specific aims and address the specified hypotheses.

*Aim 1:* Refine alpha-i components by conducting focus groups with small business owners, YPAO providers, and parents and guardians of the youth from low-income, predominantly minority neighborhoods. Results of the qualitative analysis will inform final tailoring of the intervention to create the beta-i that will be tested in aim 2.

*Aim 2:* Determine the effect of the beta-i on small business support for YPAOs by conducting a cluster randomized controlled trial with randomization at the neighborhood level. The intervention neighborhoods (n=10) will receive the beta-i, whereas the control neighborhoods (n=10) will be provided a standard practice intervention for a period of 1 year.

*Hypothesis 1:* The beta-i will result in a significantly greater increase in the percentage of small businesses providing support (eg, monetary donations) for YPAOs than a standard practice intervention.

*Hypothesis 2:* The US dollar equivalent of all types of support (monetary, goods/services, and time) donated for YPAOs by small businesses exposed to beta-i will be greater than that donated by small businesses exposed to the standard practice intervention.

*Aim 3:* Examine the impact of the increased small business support for YPAOs on YPAO utilization by the youth. The primary outcome will be the percent change in the number of youths participating in YPAOs from baseline to follow-up.

*Hypothesis 3:* The percent increase in youth participants from baseline to follow-up will be significantly greater at YPAOs in the treatment neighborhoods receiving support from small businesses than at YPAOs in the control neighborhoods.

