#### Approach to Analysis

Before developing statistical models, an examination of the univariate distribution of variables will be conducted (eg, scatter plots). Statistics, such as means or proportions, standard errors, ranges, and estimates of skewness and kurtosis will be derived for the overall samples and stratified by condition and characteristics of small businesses and YPAOs using SAS 9.4 and used as guidelines in the application of both bivariate and multivariate analyses [85]. Data transformation procedures (eg, logarithmic) may be applied to quantitative variables whose distribution shows considerable departure from normality. In the case of discrete variables, results will provide guidance in recoding these variables appropriately for statistical modeling. Graphical data will be developed to provide visual comparisons of changes across time between the 2 study conditions on key measures of small business involvement and YPAO utilization by the youth. The primary outcome will be examined using a mixed-model, nested logistic regression analysis of proportions where (1) businesses are nested in neighborhoods and (2) neighborhoods are treated as a nested random effect within treatment conditions. Generalized models will be used to explore potential mediators/moderators of outcomes. For example, a model will be constructed with experimental condition (treatment vs control), neighborhood variables (eg, median income), and business variables (eg, number of employees and years in business) as the independent variables and mean percent change in small businesses donating as the dependent variable. In another model, donation amounts equated to US dollars will be used as the dependent variable. To accommodate the complex nature of the research design, the SAS PROC GLIMMIX and SAS PROC MIXED (SAS, 2015) procedures will be used.

### Sample Size Determination for Aim 3

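### The stated 86% power matches a large-sample calculation; the neighborhood-level degrees of freedom implied by the planned model give about 82% on the same inputs

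*Protocol article*

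**What the plan says.** The Power Analysis section takes its effect from earlier work, in which "a 27% versus 8.0% increase in support for community physical activity initiatives by small businesses not supporting them at baseline was observed" in treatment and control neighborhoods respectively. The final power model uses 10 neighborhoods per condition, "10 small businesses nested in each neighborhood, a difference in proportions of 19 percentage points, and an ICC of 0.05". The result is: "It was determined that having 10 neighborhoods per condition would give us a statistical power of 86% to yield a statistically significant result". The section says that the formulas allowed for the number of neighborhoods and used variance estimates from preliminary studies. It prints no formula, reference distribution, alpha or sidedness, and it does not show those variance estimates. After losses it expects 104 businesses per condition.

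The Approach to Analysis section specifies a mixed logistic model for the primary outcome in which "neighborhoods are treated as a nested random effect within treatment conditions", fitted in SAS with PROC GLIMMIX and PROC MIXED. It prints no degrees of freedom. The Study Neighborhood Identification section says that neighborhoods were randomized in pairs, but the model has no pair term.

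**The concern.** Condition is assigned to whole neighborhoods, and there are only 20 of them. When neighborhoods are random within condition, the treatment effect is judged against variation between neighborhoods, and that variation is itself estimated from 20 units. A design effect inflates the variance for clustering, but it does not allow for the small number of clusters. That allowance comes from using a t reference with neighborhood-level degrees of freedom. If the printed power came from a normal reference, or from degrees of freedom counted in businesses, it describes a slightly more powerful test than the planned model provides. At stake are the accuracy of the headline power figure and the margin it appears to leave above 80%. The same reference would also carry over into any later recalculation.

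**Working it through.** **Inputs.** From the Power Analysis section: 10 neighborhoods per condition, m = 10 businesses per neighborhood (100 per condition), 27% versus 8% (difference 0.19), ICC 0.05. Allocation is 10 to 10 neighborhoods (Objectives section). Assumed, because not printed: alpha 0.05 two-sided, and binomial variances p(1 - p).

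**Step 1: standardized difference.**
- Design effect = 1 + (m - 1) x ICC = 1 + 9 x 0.05 = 1.45; effective sample size = 100/1.45 = 68.97 per condition.
- Variance sum = 0.27 x 0.73 + 0.08 x 0.92 = 0.1971 + 0.0736 = 0.2707.
- SE = sqrt(0.2707 x 1.45/100) = 0.0627.
- Difference/SE = 0.19/0.0627 = 3.03 (3.033 unrounded).

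**Step 2: reproduce the stated figure.**
- Normal reference: Phi(3.033 - 1.960) = 85.8%, which rounds to the printed 86%.
- t reference with business-level df, 200 - 2 = 198: 85.5%.
- Other normal versions lie close by: arcsine scale 86.2%, pooled null variance 84.3%.

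**Step 3: the df implied by the planned model.** With neighborhoods random and nested in condition, the condition effect has 20 - 2 = 18 df. The 18 is derived here; it is not printed. The critical value is 2.101 instead of 1.960.

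| Reference (two-sided 5%, unpooled binomial variance) | Critical value | Power |
|---|---|---|
| Normal | 1.960 | 85.8% |
| t, 198 df (businesses) | 1.972 | 85.5% |
| t, 18 df (neighborhoods) | 2.101 | 81.8% |
| t, 9 df (pairs kept, no gain from matching) | 2.262 | 77.0% |

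**Step 4: robustness.**
- With 104 businesses per condition, m = 10.4 and the design effect is 1 + 9.4 x 0.05 = 1.47. Difference/SE = 3.072, giving 86.7% under the normal reference and 82.8% with 18 df.
- Arcsine effect with 18 df: 82.2%. Pooled variance with 18 df: 79.3% to 80.6%, against 83.6% to 84.3% for the matching normal versions.
- Simulated beta-binomial data at the stated inputs, analyzed with a neighborhood-level t test (200,000 runs): 82.3% with the 18-df cutoff and 85.7% with 1.96.
- Simulated random-intercept logistic model (6,000 trials): 86% with a z test and 83% with t on 18 df.

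On binomial variances, no two-sided 18-df calculation among these reaches 86%. The gap is 3 to 4 points throughout.

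**The case against.** The strongest reply is that the cause is inferred. The article prints no formula, alpha or sidedness, and its preliminary variance estimates are not shown. This stands, and it limits the claim. With 18 df, a variance 11% below the binomial value gives difference/SE = 3.033/sqrt(0.89) = 3.215 and power of 86.0%, so the unseen input alone could produce the printed figure. Nor is 1.96 the only route to 86%, since 198 business-level df also rounds close to it. One-sided testing is a weaker explanation. The matching one-sided normal calculation gives 91.7%; a one-sided log-odds test with 18 df comes nearer, at 84.9%, but nothing in the document points to one-sided testing.

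A second reply is that 86% is the correct output of a common design-effect formula, so this is a small-sample refinement and not faulty arithmetic. That is fair, but the refinement follows from the model that the article itself names.

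A reader might infer that the primary test will have an inflated type I error. With 20 neighborhoods, a 1.96 cutoff does reject somewhat too often under the null: 5.6% to 6.4% in simulation, against 3.7% to 4.9% with 18 df. But the article never says that it will test against z, so this is a conditional warning and not a fault in the plan. A reader might also infer that the trial is underpowered. The documents do not support that on this point alone. Figures of 79% to 81%, obtained by letting neighborhood samples vary in size, rest on assumed variation, because the article gives no per-neighborhood counts.

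**Conclusion.** The point holds in a limited form. On the printed inputs, with binomial variances and an assumed two-sided 5% test, 86% agrees with a large-sample calculation, whereas the neighborhood-level df of the planned nested model give about 82%. Type II error is then about 18% and not 14%. The overstatement is 3 to 4 points. By itself it does not bring power below 80% and calls for no change to the design. That the sponsor used a large-sample formula is a reasonable inference from the match, not something the article states. The 18 df also depend on leaving the pairs out of the model. If they are kept, the df fall to 9 and power is about 77% before any gain from matching, which the document gives no basis for estimating.

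**What to change.** In the Power Analysis section, restate the power with a t reference on the neighborhood-level df of the primary test, and print alpha and sidedness. On the stated inputs this is about 82% with 18 df. Decide whether the randomized pairs enter the primary model; if they do, use 9 df (about 77%) and state any gain assumed from matching. If the preliminary variance estimates differ from binomial, show them. In the Approach to Analysis section, add one line fixing the same denominator df for the condition test in PROC GLIMMIX.

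Use the same reference in any recalculation, whether for the actual per-neighborhood counts among the 244 businesses surveyed at baseline or for the baseline non-supporters who are eligible for the primary outcome. The figure of about 82% still assumes 10 analyzable businesses in every neighborhood.

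The cost is one less favorable figure and one added line. No more neighborhoods or businesses are needed.
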